## Background

Preeclampsia is a common obstetrical complication, affecting 2%-8% of all pregnancies [1, 2]. It accounts for maternal and infant morbidity and mortality worldwide. Since first case report in 1978 [3], prevention of preeclampsia with aspirin has been studied for decades [4]. Its effect is inconsistent in abundant case–control, prospective cohort, or meta-analysis studies [5–12]. In the trial of low-dose Aspirin in the Prevention of Pre-Eclampsia in China (APPEC), the strategy of a dose of 100 mg aspirin daily in preventing preeclamapsia among high-risk women screened with maternal risk factors did not reduce the incidence of preeclampsia, indicating further consideration combining with maternal biophysical parameters [13]. In 2019, the International Federation of Gynecology and Obstetrics (FIGO), has recommended a Bayes theorem-based model, which integrated with maternal risk factors, mean arterial pressure (MAP), uterine artery PI (UTPI) and serum placenta growth factor (PlGF) [14]. It has provided a new era for the preeclampsia risk prediction.

Despite clear recommendations in clinical guidelines of preeclampsia risk prediction, most evidence are based in Caucasians or African Americans [5, 9–12, 15]. In the randomized controlled study-the Aspirin for Evidence-Based Preeclampsia Prevention trial based in European population, the incidence of preterm preeclampsia has been reduced by 62% for women at high risk of preeclampsia, when they take aspirin at a daily dosage of 150 mg initiated before 16 gestational week [9]. However, studies addressing the effectiveness of this Bayes theorem-based model among Chinese pregnant women are limited. There was a prospective, non-intervention, multiple centered trial conducted among 10,935 Asian women, but only approximately 700 women from Jiangsu and Yunnan province in mainland China have been recruited [16]. Thus, the effectiveness of this model across China have not been well investigated. Considering varied incidence rates among women of different race and genetic susceptibility, it is of importance to verify the performance of this Fetal Medicine Foundation (FMF) Bayes-theorem based method for Chinese women.

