### Measures

#### Primary outcomes

The primary outcomes for this trial is the incidence of preeclampsia. The diagnosis will be collected during pregnancy period, at delivery and till 42 days postpartum, including the detailed onset time and severity. Related complications will also be recorded such as eclampsia and HELLP syndrome.

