#### Sample size

It is expected that 15,000 eligible pregnant women in all eighteen sectors will register at antenatal visit in first trimester (based on previous annual delivery number in each sector) during the first 18-month enrollment period of this trial. Assuming 70% of invited women will agree to participate in this project, approximately 10,500 women will be enrolled in this study.

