### Statistical analysis

Statistical analyses will be conducted on an intention-to-treat basis. Primary and secondary outcomes will be analyzed using a logistic mixed model to determine the significance of the between group difference in the incidence of preeclampsia and other complications, with adjustment for the effect of the estimated risk of preeclampsia at screening and the participating center. Prespecified analyses will be performed in subgroups that were categorized according to the estimated risk of preterm preeclampsia and history of preeclampsia, and a post hoc subgroup analysis according to the participating centers. A sensitivity analysis will be performed to take into account the effect of withdrawal of consent and loss to follow-up. Kaplan–Meier estimates of the cumulative incidence of preeclampsia according to trial group will be conducted, in which deliveries that were not with preeclampsia were excluded. The statistical software package R was used for data analyses.

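### As worded, the Kaplan–Meier display keeps only women with preeclampsia, so its curves reach 100% in both groups and cannot show incidence; the primary model is unaffected

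*Protocol article*

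**What the plan says.** All of the relevant analysis text is in the Statistical analysis section of the protocol article. One sentence there names both the target and the analysis set: "Kaplan–Meier estimates of the cumulative incidence of preeclampsia according to trial group will be conducted", "in which deliveries that were not with preeclampsia were excluded".

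Three other statements bear on it:

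- The same section opens with "Statistical analyses will be conducted on an intention-to-treat basis".
- The test of the treatment effect is a separate item: "Primary and secondary outcomes will be analyzed using a logistic mixed model to determine the significance of the between group difference".
- Under Primary outcomes, the endpoint is preeclampsia incidence, and its ascertainment runs past delivery: "The diagnosis will be collected during pregnancy period, at delivery and till 42 days postpartum, including the detailed onset time and severity".

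Nowhere does the article say that women who deliver without preeclampsia stay in this analysis as censored observations, or that they are handled as having a competing event.

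**The concern.** A cumulative incidence needs everyone at risk in the denominator. Taking out women because they did not have the event selects on the outcome. Every woman left is a case, and the curve becomes the distribution of onset time among cases. The sentence therefore names one quantity and prescribes a data set that yields another.

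This is the only time-to-event display that the article describes for the primary outcome. Produced as written, it could show two nearly identical curves when the intervention had halved preeclampsia. It could also show separated curves because of onset timing alone, in groups that randomisation no longer makes comparable.

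**Working it through.** **Inputs.** From the article: 15,000 eligible women and 70% participation (Sample size); preeclampsia "affecting 2%-8% of all pregnancies" (Background); outcome ascertainment to 42 days postpartum (Primary outcomes). The 2% to 8% is a general background figure, not a design assumption. The intervention-group rates used below are assumptions.

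**The plan's own figure.** 15,000 × 0.70 = 10,500 women, as the article states. The argument does not depend on this number; it only gives the scale.

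**Algebra.** Let a group have N women, of whom n become cases, and ignore early loss. The Kaplan–Meier estimate falls by the factor 1 − 1/(number at risk) at each event.

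- Cases only: after k events, S = (n−1)/n × (n−2)/(n−1) × … × (n−k)/(n−k+1) = (n−k)/n. So 1 − S = k/n, and at the last event (k = n) it is 1.
- All women kept to the end of follow-up: 1 − S = k/N, ending at n/N, the incidence.

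The case-only curve is the all-women curve divided by the group's own incidence. The division removes exactly the quantity that the figure is meant to show. No assumed event rate is needed for this.

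**Share of women dropped.** At 2%: 10,500 × 0.02 = 210 kept and 10,290 dropped (98%). At 8%: 10,500 × 0.08 = 840 kept and 9,660 dropped (92%). A group with incidence below 2% would lose slightly more.

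**Simulation check.** There were 105,000 women per group, with the same onset-time distribution in both groups (mean 36.5 weeks, SD 3, limited to 20–46), delivery at mean 39 weeks (SD 1.7, limited to 24–42), and follow-up to 6 weeks after delivery.

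| Assumed true incidence | Cases only, at 37 weeks | Cases only, final | All women, censored at end of follow-up, final |
|---|---|---|---|
| 2% vs 1% | 0.558 vs 0.556 | 1.000 vs 1.000 | 2.0% vs 1.0% |
| 5% vs 3% | 0.565 vs 0.560 | 1.000 vs 1.000 | 5.1% vs 3.0% |
| 8% vs 4% | 0.562 vs 0.568 | 1.000 vs 1.000 | 8.0% vs 4.0% |

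Two further pairs (2% vs 1.24% and 8% vs 3.04%) also ended at 1.000 in both groups under the stated rule.

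**Does loss to follow-up rescue the rule?** If 5% of women are lost and kept as censored while other non-cases are still removed, the final values remain 1.000. For 2% vs 1%, the 37-week values become 0.425 and 0.358. The curves now separate, but neither is near an incidence; the lost women act as an accidental denominator, so the levels depend on how many are lost.

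**Would censoring at delivery do?** In the same simulation, censoring non-cases at delivery while counting later-onset cases also gave a final value of 1.000 in every scenario. After the last non-case has delivered, only future cases are at risk. Women without preeclampsia therefore have to stay at risk through the postpartum window.

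The simulation had no competing events, so it supports censoring at the end of follow-up. It does not test the competing-event part of the fix.

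**The case against.** The strongest reply is that the exclusion is loose wording. The same sentence calls the target a cumulative incidence by trial group, which a case-only set cannot supply, so the authors may have meant that these women are censored or not counted as events. That is plausible, and it cannot be settled from the article. It lowers confidence that women would really be dropped. It does not make the sentence right, because removal and censoring give very different curves and only removal is stated.

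The second reply is that the curves are supportive. This stands. The article assigns the primary and secondary outcomes to a logistic mixed model, and no test, decision rule or sample size rests on the Kaplan–Meier estimate. A reader might infer that the trial's effect estimate or its conclusion is compromised; the documents do not support that.

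The third reply is that a case-only curve is not empty, and this also stands. A reader might infer that every trace of a treatment effect is lost. In fact the effect on incidence is lost while differences in onset timing can still appear, and the article records onset time. An earlier or later shift among cases could be real, but it is conditional on having become a case and should not be presented as incidence.

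**Conclusion.** The point holds for the sentence as written. Followed literally, it gives a final value of 1 in each group at any true incidence, and what is displayed is onset timing among cases. At 2% to 8% incidence about 92% to 98% of women leave the analysis because of their outcome, which conflicts with the stated intention-to-treat basis.

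The end value of 1 is algebraic. The near-coincidence of the curves before the end rests on equal onset timing in the two groups and on no lost women being retained. The share dropped rests on the background incidence applying to this population.

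The reach is limited to one supporting descriptive display. The logistic mixed model and the enrolment figure are untouched. It is certain that the text needs correcting; it is not certain that the analysts intend to remove these women.

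**What to change.** Replace the exclusion clause with wording such as:

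> All analysed women are included in the risk set from enrolment. Women without preeclampsia remain at risk through delivery to 42 days postpartum and are censored at the end of follow-up, or at loss to follow-up. Events that preclude preeclampsia, such as early pregnancy loss or maternal death, are treated as competing events (Aalen–Johansen). The curves are descriptive because they are not adjusted for period or cluster.

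Delivery without preeclampsia should not itself be the competing event. That would end a woman's risk at delivery and lose postpartum-onset cases that the primary outcome counts. If the authors want onset timing among cases as well, it should be a separate display labelled as conditional on being a case.

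The cost is in effect one sentence in the analysis section. Onset time and outcomes to 42 days are already collected, so no new data are needed, and the article already provides for protocol modifications to be updated on the registry.

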### Research trial governance

The advisory committee of this trial is consisted of obstetricians, statisticians, policy makers and clinical experts with expertise related to preeclampsia. The project team will implement strategies and collect data according to study protocol. Local clinical experts of all the eighteen participating sectors will provide advice and tailor the trail implementation strategies based on sector-specific requirements.

### Trial discontinuation or modification

This trial has been approved by the Research Ethics Committee of Obstetrics and Gynecology Hospital of Fudan University (2021–48). Each hospital of all the eighteen sectors will apply for ethic approval from their own hospital before the trial initiation. There are no criteria for trial discontinuation as it is not anticipated that any events would occur that would warrant discontinuing the trial. The researchers will notify all the unforeseen adverse events and timely report to the Research Ethics Committees of Obstetrics and Gynecology Hospital of Fudan University and of the local sector. The trial has been registered at Chinese Clinical Trial Registry (ChiCTR2100043520), and protocol modifications and deviations from original protocol will be updated.

## Discussion

Despite clinical guideline recommendations based on high-quality randomized controlled in Europe, effectiveness of the Bayes-theorem based preeclampsia risk prediction model in first trimester among Chinese women is limited. There is an urgent need for evaluate its effectiveness in reducing the risk of preeclampsia among Chinese pregnant women.

This will be the first randomized controlled trial to evaluate the effectiveness of the Bayes-theorem based risk model in China. The stepped-wedge design is logical, feasible and ethical in the setting of eighteen sectors providing maternal antenatal services. The key elements of trial are random allocation across the sectors, comprehensive data collection and management protocol.

If positive preventive effect in clinical practice are found, this evidence will support health service adoption of this risk prediction model to reduce the risk of preeclampsia among Chinese women.

## Data Availability

The datasets during the current study are available from the corresponding author on reasonable request.

## Abbreviations

APPEC: Aspirin in the Prevention of Pre-Eclampsia in China
FIGO: The International Federation of Gynecology and Obstetrics
MAP: Mean arterial pressure
UTPI: Uterine artery PI
PlGF: Serum placenta growth factor
FMF: Fetal Medicine Foundation
ChiPERM: Preeclampsia risk prediction model for Chinese pregnant women
CRL: Crown rump length
sFlt-1: Soluble fms-like tyrosine kinase 1
NICU: Neonatal intensive care unit
HELLP syndrome: Hemolysis, elevated liver enzymes and low platelet
